#### Health behavior and health literacy

The average alcohol consumption is assessed separately for beer and cider, wine, and distilled beverages using five-point scales. For beer and cider, the response options range from zero (not at all) to four (more than 12 bottles a week), for wine, from zero (not at all) to four (more than two bottles a week), and for distilled liquor, from zero (not at all) to four (more than four bottles a month). In addition, we ask participants whether other people have been worried about their alcohol consumption or whether others have suggested drinking less. The response options are: one (never), two (yes, but not during the last year), and three (yes, during the last year). Smoking history is assessed by asking whether participants smoke or have smoked daily or almost daily at least for a year. Past smokers are asked to specify the age at smoking cessation [27].

Perceived own role in health behavior is assessed with three structured questions. Participants are asked whether they believe they can contribute to maintaining their health with response options: one (yes, I believe my contribution is very important), two (yes, I think my contribution matters), and three (no, I don’t think my contribution matters). Participants are asked whether they do something for maintaining or promoting their health, and to specify their act from a seven-item list: to exercise or to be physically active, to eat healthy, to try to quit smoking or decrease smoking, to take care not to drink too much alcohol, to take care not to work too much, to ensure sufficient sleep, and something else.

Nutritional status and habits are assessed using the abbreviated questionnaire Seniors in the Community: Risk evaluation for eating and nutrition (SCREEN II-AB; The SCREEN II questionnaire is the copyright of [name]). It is a valid and a reliable measure for detecting older people at risk for impaired nutritional status [99, 101]. The questionnaire consists of eight items assessing food habits and risk factors for malnutrition. The response scores of each item ranges between zero and four (items on fruit and vegetable servings, fluid intake, company with meals, and meal preparation) or between zero and eight (items on weight change, skipping meals, appetite, and difficulty swallowing). A sum score will be calculated (range 0–48), with lower scores indicating higher nutritional risk [99].

Health literacy is measured with the short version of the European Health Literacy Survey Questionnaire (HLS-EU-Q16). The short version of the HLS-EU-Q includes 16 items, covering the domains of health care, disease prevention and health promotion [102]. Participants are asked to rate the perceived difficulty in different tasks of accessing, understanding, appraising and applying health information. The response options are: one (very difficult), two (fairy difficult), three (fairly easy), and four (very easy). A general index of health literacy will be calculated for respondents with at least 80% of the health literacy questions completed using the formula [103]:

$$ Index=\left( mean-1\right)\ast \left(\frac{50}{3}\right) $$

The final index score will range from 0 to 50, with higher scores representing better health literacy. The score can be divided into inadequate (0–25), problematic (> 25–33), sufficient (> 33–42) and excellent (> 42–50) health literacy [104].

#### Mobility

Life-space mobility reflects actual mobility performance in daily life and is assessed with the University of Alabama at Birmingham Study of Aging Life-Space Assessment (LSA) [105, 106], which has good test-retest reliability. The LSA comprises 15 items and assesses mobility through the different life-space levels (bedroom, other rooms, outside home, neighborhood, town, beyond town), which the participant reports having moved through during the 4 weeks preceding the assessment. For each life-space level, participants are asked how many days a week they attained that level and whether they needed help from another person or from assistive devices. A composite score will be calculated (range 0–120), reflecting the spatial area through which a person moves, the frequency of movement and the need for assistance. Higher scores indicate greater life-space mobility.

The use of different transportation modes is assessed by asking how often participants drive a car, travel by car as a passenger, use public transportation such as a bus or a train, and use taxi or Special Transportation Services [27]. The response options are: one (daily or almost daily), two (a few times a week), three (a few times a month), four (a few times a year), five (less than once a year), and six (never). Participants who answer that they never drive a car are asked to specify whether they have never driven a car or whether they have stopped driving a car.

Self-reported mobility limitations are assessed as perceived difficulty in walking 500 m and two kilometers, and mounting a flight of stairs [107, 108]. The response options are: one (able to manage without difficulty), two (able to manage with some difficulty), three (able to manage with great deal of difficulty), four (able to manage only with help of another person), and five (unable to manage even with help). For each task, those who report being able to manage without difficulty are asked whether they have modified their way of performing the task (mobility task modification) [107]. The question is “Have you noticed any of the following changes in your ability to walk 2 km/500 m/mount a flight of stairs?” The potential modifications are: having slowed down the pace, resting in the middle of performing the task, using an assistive device, and having reduced the frequency of performing the task, and the response options are: one (yes) and two (no). In addition, we enquire whether the person has given up doing the task or if the person experiences tiredness when doing the task. For each task, there is an additional open-ended question about other changes in the ability to perform the task. The questions regarding task modification identify older people in an intermediate phase between intact mobility and manifest mobility limitation [108]. In addition, participants are asked whether they use the assistive devices listed: walking stick, crutches, Nordic walking sticks, rollator, kicksled/kickcycle, wheelchair, electric scooter, other.

Fear of falling is assessed by the question “Are you afraid of falling?” with response options: one (never), two (occasionally), three (often), and four (constantly) [27]. Fall history is assessed using the question “Have you fallen or slipped during the previous year?” with response options: one (no), two (yes, outdoors), three (yes, indoors), four (yes, both indoors and outdoors). Fallers are asked whether they have fallen once or multiple times, and whether any fall resulted in an injury, which required treatment by a physician.

#### Other aspects

The home interview and the laboratory assessments are completed by asking participants whether they want to share any thoughts and feelings about the interview or assessments with open-ended question (debriefing). After the home interview, participants are also asked whether something out of the ordinary has recently happened in their lives that they feel has influenced their answers. Participants can freely share their thoughts on such occasions. If necessary, messages are registered.

Information on age and sex are drawn from the population register. Life years will be calculated in 2028, approximately 10 years after the initial assessments. Death dates will be requested from the Population Register. Survival time will be calculated from the day of the home interview to the day the participant died [9]. Participants not known to have died or lost to the follow-up will be given a survival time of 10 years.

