### Recruitment process and inclusion criteria

The population register is used to target 75-, 80- and 85-year old people living in Jyväskylä, Finland, in postal areas within a 10 kilometer radius of the city center or within reach of local public transportation. The population-based study is targeted to include 1000 participants in total. Based on an estimated participation rate of 50% in previous studies, a sample of at least 2000 people would be needed. Participants aged 75 years old are recruited since September 2017, and in 2018, those aged 80 years and 85 years will be recruited. Samples are drawn from population registers shortly before the initiation of the assessment of each age-cohort. Inclusion criteria for the population-based study are age 75, 80 or 85 years, and living independently in the recruitment area (Jyväskylä). Exclusion criteria are unwillingness to participate and inability to communicate.

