Self-reported use of alcohol (four items)	x	–	–	–	–	
Self-reported smoking history (single items)	x	–	–	–	x	
Perceived own role in health behavior (three items)	x	–	–	–	x	
Nutritional status and habits (eight-item Abbreviated Screen II)	x	–	–	–	–	[99]
Health literacy (16-item HLS-EU-Q16 questionnaire)	–	x	–	–	–	[102]
Mobility						
Life-space mobility (15-item LSA questionnaire)	–	x	–	–	–	[105, 106]
Transportation modes (four items)	x	–	–	–	–	[111]
Self-reported mobility limitation (three items)	–	x	–	–	–	[107, 108]
Self-reported mobility task accommodation (three items)	–	x	–	–	–	[107]
Assistive device use (eight items)	–	x	–	–	–	[27]
Fear of falling (single item)	x	–	–	–	–	[27]
Fall history (three items)	x	–	–	–	–	
Other						
Debriefing (two items)	–	x	x	–	–	
Age and sex	–	–	–	–	x	
Life years	–	–	–	–	x	[9]

For each assessment, the point of data collection is indicated: part of the postal questionnaire (P), part of the home interview (H), part of the assessment in the research center (R), and part of the activity surveillance (S). In addition, availability of the measure in the historic cohort is indicated (C)

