### Data management and quality assurance

#### Data management

The University of Jyvaskyla fully owns the research data. Consent forms and paper questionnaires are stored in locked cabinets in a project researcher’s office. Digital data are stored on computer drives of the Information Management Center of the University of Jyvaskyla. All datasets are pseudonymized. The research data are managed by AGNES research team members appointed for this task. The key identifying participants is stored separately from data files and only accessible to designated research team members. In 2023, we will re-evaluate the need to store the identification key. For all participants, once vital status is checked in 2028, the identification key will be destroyed. All research team members can use the pseudonymized datasets for research and teaching for the time when they are employees of University of Jyvaskyla.

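### The fixed 10-year survival time does not match a follow-up of about 9.0 to 11.3 years, and deaths are not cut off at the same horizon (low severity)

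*Protocol article*

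**What the plan says.** All of this is in the protocol article.

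- **Time origin and deaths** (Other aspects): "Survival time will be calculated from the day of the home interview to the day the participant died". The source is the register: "Death dates will be requested from the Population Register". No upper limit is set on the time of a death.
- **Everyone else** (Other aspects): "Participants not known to have died or lost to the follow-up will be given a survival time of 10 years".
- **When it is calculated** (Other aspects): "Life years will be calculated in 2028, approximately 10 years after the initial assessments". No day or month is given.
- **Entry** (Recruitment process and inclusion criteria): "Participants aged 75 years old are recruited since September 2017, and in 2018, those aged 80 years and 85 years will be recruited".
- **One check, then no more linkage** (Data management): "For all participants, once vital status is checked in 2028, the identification key will be destroyed".

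Table 1 marks life years as available in the 1989–90 cohort. The measure does not appear under Project aims, Main outcomes or Statistical analyses.

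**The concern.** Each statement is reasonable alone, but together they do not give every participant 10 observed years. The clock starts on a personal date and the register is read on one calendar date, so follow-up differs between people. It differs systematically by age, because the age groups enter at different times.

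Three things follow. A check that comes before someone's 10-year date credits them with time nobody has observed. A check that comes after it lets a late death score higher than a survivor. And the sentence on those lost to follow-up can be read in two ways, one of which counts lost people as having lived the full 10 years.

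At stake are the ordering and age comparability of a survival variable that may be used later. Timing matters most, because deaths missed by an early extract cannot be linked once the key is gone.

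**Working it through.** **1. Follow-up available at the check**

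Inputs from the document: entry of 75-year-olds from September 2017, entry of 80- and 85-year-olds in 2018, check at some date in 2028. Assumptions: the 75-year-olds were enrolled by the end of 2017, and home interviews took place in the recruitment period. Follow-up = check date − interview date.

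| Check date | Age 75 | Ages 80 and 85 |
|---|---|---|
| 1 January 2028 | 10.0–10.3 years | 9.0–10.0 years |
| 1 July 2028 | 10.5–10.8 years | 9.5–10.5 years |
| 31 December 2028 | 11.0–11.3 years | 10.0–11.0 years |

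The plan's figure of roughly 10 years is right as an average. It is not right for each person: the overall range is 9.0 to 11.3 years. Only a check at the end of 2028 gives every 2018 entrant a full 10 years.

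**2. Early check: unobserved time credited**

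The document gives no mortality rates, so I assume a Gompertz hazard with slope b = 0.11 per year and a hazard at age 75 of h75 = 0.015, 0.025 or 0.035 per year:

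S(t) = exp{−(h/b)(e^(bt) − 1)}, with h = h75 · e^(b(age − 75)).

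If everyone in a group has follow-up C < 10 and those alive are set to 10, the 10-year mean is overstated by

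∫₀^C S dt + (10 − C)·S(C) − ∫₀^10 S dt.

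- C = 9.0 (worst case): 0.024–0.032 years at age 80 and 0.026–0.031 at age 85.
- C = 9.5: 0.006–0.008 years at both ages.
- Check at the end of 2028: zero.

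Hand check at age 80 with h75 = 0.025: S(9) = 0.514 and S(10) = 0.454, so the overstatement is about (0.514 − 0.454)/2 = 0.030 years, which agrees.

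**3. Late check: order reversed**

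A person interviewed on 1 September 2017 who dies at the end of June 2028 scores 10 years and 10 months, about 10.8. A person interviewed the same day and still alive scores 10.0. At the extreme (interview on 1 September 2017, check on 31 December 2028), the share of 75-year-olds dying between 10 and 11.3 years is S(10) − S(11.3) = 4.6% to 7.2% under the assumed hazards. That is an upper limit for the group.

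The problems in steps 2 and 3 pull in opposite directions. Waiting until the end of 2028 removes the first and makes the second largest. On 1 January 2028 the first is largest, and the second remains only for 75-year-olds with up to 10.3 years.

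**4. People lost to follow-up**

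Reading (a): those neither known dead nor lost get 10 years, and the lost have no rule. Reading (b): those not known dead, and also those lost, get 10 years. Under (b), with loss assumed spread evenly over the 10 years, the results are:

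| Age | Over-credit per lost person | Group mean, 2% lost | Group mean, 5% lost |
|---|---|---|---|
| 75 | 0.42–0.90 years | 0.008–0.018 | 0.021–0.045 |
| 80 | 0.69–1.40 years | 0.014–0.028 | 0.035–0.070 |
| 85 | 1.11–2.06 years | 0.022–0.041 | 0.055–0.103 |

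The group-mean columns are the loss share times the per-person figure (for example 0.05 × 2.06 = 0.103). The document gives no loss rate; 2% and 5% are assumptions.

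**The case against.** The best defence is that a 10-year administrative limit is an ordinary way to code survival. For someone known to be alive at 10 years, writing 10 is correct for a restricted mean, and correct for censoring if an indicator is kept. The article does not say that survivors are treated as deaths or that no indicator exists, and the choice of survival model can be left to an analysis plan. That stands. It does not cover the rule that is written down: the limit applies to survivors but not to deaths, and nothing ensures that each person is observed for 10 years before receiving the value.

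Four stronger readings are tempting and not supported.

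- *The rule biases the comparison with the 1989–90 cohort.* The document does not say how life years is calculated there. If the same limit is used, the horizon is common.
- *Everyone lost is credited with 10 years.* That is only reading (b), and register-based deaths may keep loss low.
- *The error is large.* With assumed hazards of 0.14 and 0.25 per year for the 80- and 85-year-old entrants near year 10, a check at the start of 2028 and a mean gap of half a year, 1 − exp(−0.14 × 0.5) = 6.8% and 1 − exp(−0.25 × 0.5) = 11.8% of survivors would not reach the 10 years given to them; with a full one-year gap, 13.1% and 22.1%. These are shares of survivors at the earliest possible check, not bias in life years. Nor is the early-check bias clearly worst at 85: fewer survive to be over-credited, and ages 80 and 85 come out nearly equal.
- *Nothing can be repaired once the key is gone.* If interview, death and extract dates are kept in the pseudonymized data, times can be recoded without the key. Only new linkage is lost.

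It is also true that no aim, listed outcome or stated analysis depends on life years.

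**Conclusion.** The point holds at low severity. The rule cannot give each participant an observed 10 years, because follow-up at the check lies between about 9.0 and 11.3 years and depends on age group. No check date in 2028 avoids both crediting unobserved time and ranking a late death above a survivor. The reversed order follows from the wording alone and needs no mortality assumption.

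The effect on means is small: about 0.03 years or less from an early check, and up to about 0.10 years at age 85 if 5% are lost and reading (b) is meant. These sizes rest on the assumed Gompertz hazards, the assumed loss, and enrolment of the 75-year-olds by the end of 2017. The study's main results are not affected, and bias against the 1989–90 cohort cannot be established from the document.

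**What to change.** Amend the life-years paragraph and the sentence on key destruction as follows:

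1. Keep each person's observed time with a death/censoring indicator.
2. Truncate deaths and survivors alike at the 10-year anniversary of that person's own interview.
3. Reword the ambiguous sentence so that people lost to follow-up have their own rule: censored at the last date known alive.
4. Request the register extract, and destroy the identification key, only after the last-interviewed participant has passed 10 years.

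The values can then go into a Kaplan–Meier or Cox analysis or a 10-year restricted mean. The cost is a few sentences and a standard method. The one practical drawback is that the extract may have to wait until the end of 2028.

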### Data management and quality assurance

#### Data management

The University of Jyvaskyla fully owns the research data. Consent forms and paper questionnaires are stored in locked cabinets in a project researcher’s office. Digital data are stored on computer drives of the Information Management Center of the University of Jyvaskyla. All datasets are pseudonymized. The research data are managed by AGNES research team members appointed for this task. The key identifying participants is stored separately from data files and only accessible to designated research team members. In 2023, we will re-evaluate the need to store the identification key. For all participants, once vital status is checked in 2028, the identification key will be destroyed. All research team members can use the pseudonymized datasets for research and teaching for the time when they are employees of University of Jyvaskyla.

#### Quality assurance

The interviewers and testers participated in a training course on interviewing techniques suitable for older people, the scales and tests, study ethics and safety as well as practice interviews and testing sessions. Manuals of operations have been prepared prior to the start of the study (September 2017) and will be updated if necessary. Computer assisted interviewing techniques are used, whenever possible. Testing sessions are periodically observed. We monitor all incoming data for consistency and organize periodic meetings with research staff.

### Statistical analyses

Non-respondent analyses will be conducted to determine differences between participants in different parts of the AGNES study and those not participating in the respective parts in order to establish potential selection bias.

Full information maximum likelihood (FIML) estimation under the assumption of data missing at random (MAR) will be used in analyzing incomplete data. Multiple imputation methods will be used to complete the dataset for efficient and valid analyses. In sum score calculations, limited numbers of missing items (e.g. one or two), will be imputed with the participant’s mean of completed items (scaling), while in some cases best available information may be used to replace missing values.

The study data to be collected will consist of a cross-sectional dataset. Path modeling and structural equation modeling will be used for multilevel analyses of environmental and individual characteristics relative to the study outcomes. The cross-sectional data will be analyzed with Bayesian methodology permitting better control of expectations generated by previous research, and interpretability of the results. Markedly non-normally distributed data will be transformed prior to inferential comparisons. For variables that cannot be successfully transformed, nonparametric methods will be used. Categorical variables will be analyzed with logistic regression or categorical response models. If the expected frequencies are too small for asymptotic assumptions, exact testing techniques will be used.

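### Filling missing items with the participant's raw mean is wrong for SCREEN II-AB, because its items have two different score ranges

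*Protocol article*

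**What the plan says.** The Statistical analyses section of the protocol article gives a general rule for incomplete sum scores: "In sum score calculations, limited numbers of missing items (e.g. one or two), will be imputed with the participant’s mean of completed items (scaling". It adds an open exception, "while in some cases best available information may be used to replace missing values", without naming a scale or a situation. The same section also plans full information maximum likelihood and multiple imputation for incomplete data.

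The section on health behavior and health literacy describes SCREEN II-AB: "The questionnaire consists of eight items assessing food habits and risk factors for malnutrition". Half of them are scored "between zero and four (items on fruit and vegetable servings, fluid intake, company with meals, and meal preparation". The other four have a maximum twice as large and are scored "between zero and eight (items on weight change, skipping meals, appetite, and difficulty swallowing". On the total it says "A sum score will be calculated (range 0–48), with lower scores indicating higher nutritional risk". It says nothing about missing items.

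Several other instruments do have a provision of their own: UJACAS, CES-D, SPPB, MMSE and HLS-EU-Q16. The general sentence therefore matters for scales without one, and SCREEN II-AB is among them.

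**The concern.** Replacing a missing item with the mean of the answered items assumes that all items are on one scale. When half the items run to 4 and half to 8, the raw mean is a blend that suits neither half. It is too large for a 0–4 item and too small for a 0–8 item.

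The error in a person's score then depends on which question was skipped. Someone who leaves out fluid intake looks better nourished than they are. Someone who leaves out appetite looks worse. Table 1 places the questionnaire in the postal form, so some skipped items are plausible. Nutrition belongs to the health behaviors that the first project aim examines as predictors of active aging.

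**Working it through.** **Inputs, all from the article.** Eight items; four with maximum 4 and four with maximum 8; total range 0–48; one or two missing items filled with the mean of the completed items.

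**Stated maximum.** 4 × 4 + 4 × 8 = 48, so the article's range is reproduced.

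**Formulas.** Let S be the sum of the k completed items and M the sum of their maxima.
- Rule as written: each missing item gets S/k, so the total is S + (8 − k) × S/k = S × 8/k.
- Range-proportional scaling: total = S × 48/M.

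The two agree for every S only if 8/k = 48/M, that is, if the completed items have an average maximum of 6. This fails whenever the missing items are all of one type.

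**Results.** Two profiles are shown: full marks on every answered item, and 75% of every maximum (3 on each 0–4 item, 6 on each 0–8 item). The 75% level is illustrative and not taken from the article.

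| Missing | k | M | Full marks (true 48) | 75% profile (true 36) | Error at 75% |
|---|---|---|---|---|---|
| one 0–4 item | 7 | 44 | 44 × 8/7 = 50.29 | 33 × 8/7 = 37.71 | +1.71 |
| two 0–4 items | 6 | 40 | 40 × 8/6 = 53.33 | 30 × 8/6 = 40.00 | +4.00 |
| one 0–8 item | 7 | 40 | 40 × 8/7 = 45.71 | 30 × 8/7 = 34.29 | −1.71 |
| two 0–8 items | 6 | 32 | 32 × 8/6 = 42.67 | 24 × 8/6 = 32.00 | −4.00 |
| one of each | 6 | 36 | 36 × 8/6 = 48.00 | 27 × 8/6 = 36.00 | 0.00 |

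Range-proportional scaling returns 36 for every row at the 75% profile: 33 × 48/44, 30 × 48/40, 24 × 48/32 and 27 × 48/36 all equal 36.

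**Impossible item values.** With one 0–4 item missing, the filled value S/7 exceeds 4 when S is above 28, so from S = 29 of 44. At the 75% profile it is 33/7 = 4.71, against a true 3 and a maximum of 4. With two 0–4 items missing, S/6 exceeds 4 from S = 25 of 40. With one of each type missing, the total agrees with proportional scaling, but the filled 0–4 item still exceeds 4 from S = 25 of 36.

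**Impossible totals.** With one 0–4 item missing, S × 8/7 exceeds 48 only when S is above 42, so at 43 or 44 of 44. With two missing, S × 8/6 exceeds 48 only when S is above 36, so from 37 of 40. When only 0–8 items or one of each type are missing, the total never exceeds 48.

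**The case against.** The strongest reply is that the sentence in Statistical analyses is a summary in a condensed article, not scoring code. It carries the word scaling in brackets. The article uses the same idea for the MMSE, which has 19 items and a 0–30 range, so its items cannot all share one maximum; there the total is scaled when parts cannot be done. Proportional scaling may be what the authors intend. There is also the exception for best available information, and multiple imputation is planned.

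Part of this stands. The intention may be right, and it cannot be claimed that the study will in fact produce totals above 48. But the words describe a raw mean of completed items, which equals proportional scaling only when all items share one range. The exception names no scale, and the sum-score sentence assigns limited missing items to the person mean rather than to multiple imputation. If proportional scaling is meant, the sentence needs to say so.

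The second reply concerns consequence, and it largely stands. Nutrition is not listed as a main or secondary outcome of the cross-sectional study. Health behavior is a secondary outcome of the cohort comparison, but Table 1 shows SCREEN II-AB as unavailable in the historic cohort. The frailty phenotype uses a single SCREEN question, not the sum. The errors also run both ways: at a common proportion f of the maximum, one missing item gives (44 × 8/7 − 48)f = +2.29f or (40 × 8/7 − 48)f = −2.29f, so the mean error is zero if both types are missing equally often at that level.

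**Conclusion.** The concern holds for SCREEN II-AB and for the rule as worded. For a person missing items of one type, the score is wrong in a known direction: upward for 0–4 items (risk understated), downward for 0–8 items (risk overstated). At 75% of every maximum the size is 1.7 points for one item and 4.0 for two, on a 48-point scale. The benchmark assumes that a missing item would lie at the same proportion of its maximum as the answered ones.

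A reader might infer more than this, and the documents do not support it:
- **That sum scores in general are distorted.** Several have their own provisions, and the raw mean does not create this problem where items share one range, as in UJACAS or CES-D.
- **That totals above 48 will be common.** They need near-ceiling answers and missing 0–4 items.
- **That the sample mean is biased or people are misclassified.** Net bias would need one item type to be skipped more often, or at different score levels. The article gives neither missing-item frequencies nor a risk cut-off.
- **That the weighted YAPS index is affected too.** The rule concerns missing items, and nothing says that YAPS sub-indices would be averaged to fill a gap.

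The consequence is therefore limited to one health-behavior predictor under the first aim. The point is still worth correcting because the stated rule can break the article's own item and total ranges.

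**What to change.** In Statistical analyses, limit raw person-mean imputation to scales whose items share one response range. For SCREEN II-AB, state one of two alternatives:
- total = 48 × (sum of completed items) / (sum of their maxima), which cannot exceed 48 and returns 48 for a full-mark respondent whichever item is missing; or
- the multiple imputation already planned, at item level and bounded to each item's range.

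If the word scaling was already meant as the first alternative, writing the formula out is enough. The cost is one sentence in the plan and one line of scoring code, with no new data.
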